#### Events that Do Not Meet the Definition of an SAE

Elective hospitalizations to simplify trial treatment or trial procedures (e.g. an overnight stay to facilitate chemotherapy and related hydration therapy application) are not considered as SAEs. However, all events leading to unplanned hospitalizations or unplanned prolongation of an elective hospitalization (e.g., undesirable effects of any administered treatment) must be documented and reported as SAEs.

#### Events Not to Be Considered as AEs/SAEs

Medical conditions present at Screening that do not worsen in severity or frequency during the trial are defined as baseline medical conditions, and are NOT to be considered AEs. These conditions should be adequately documented on the medical history form of the e-CRF. However, baseline conditions that worsen in severity or frequency during the trial should be reported as AEs.

#### Procedure for Reporting Serious Adverse Events

In the event of any new SAE occurring during the reporting period, the Investigator must immediately **(i.e. within a maximum 24 HOURS after becoming aware of the event)** inform the Sponsorby telephone, by fax or by e-mail.

When an event (or follow-up information) is reported by telephone, a written report must be sent immediately thereafter to the Sponsor by fax or e-mail.

Reporting procedures and timelines for follow-up information are the same for any new information on a previously reported SAE.

Once notified of a possible SAE, the Investigator/Reporter must complete the SAE Report, following specific instructions (i.e., the SAE Report Completion Instructions to be provided by the Sponsor) and send it directly to the Sponsor’s Global Drug Safety department by electronic mail or fax, using the dedicated e-mail address and fax numbers specified below:

e-mail: [[contact]](mailto:[contact])

[contact] (international toll-free number)

[contact] (US sites)

For any new SAEs, the following minimum information is required in the initial notification of the Sponsor:

- Clear identification of the Investigator/Reporter, with full contact information;
- Subject identification details (protocol number, site number, subject’s initials, and date of birth);
- Medicinal Product administration details (doses and dates);
- Diagnosis of the event, with the description (or a brief description of signs/symptoms/clinical course, if the diagnosis is not available) and the date of onset;
- Reason(s) for considering the event serious; and
- Relationship of the event with the drug or with the trial procedure (i.e., the causality according to the Investigator) [(see Section 7.9.1.4)](#_Grading_the_Relationship).

All written reports should be transmitted on the SAE Report,which must be completed by the Investigator following specific completion instructions. Relevant pages from the e-CRF may be provided in parallel (e.g., medical history, concomitant medications). In all cases, the information provided in the SAE Report must be consistent with the data on the event that are recorded in the corresponding sections of the e-CRF.

The Investigator/Reporter must respond to any request for follow-up information (e.g. additional information, outcome and final evaluation, specific records where needed) or to any question the Sponsor may have on the SAE within the same timelines as described for initial reports. This is necessary to permit a prompt assessment of the event by the Sponsor and, as applicable, to allow the Sponsor to meet strict regulatory timelines associated with expedited safety reporting obligations.

Requests for follow-up will usually be made by the responsible Monitor, although in exceptional circumstances the Global Drug Safety department may contact the Investigator directly to obtain clarification or to discuss a particularly critical event.

#### Safety Reporting to Regulatory Authorities, Investigators and Institutional Review Boards

The Sponsor will send appropriate safety notifications to regulatory authorities in accordance with applicable laws and regulations.

The Investigator must comply with any applicable institution-specific requirements related to the reporting of SAEs (and in particular deaths) involving his/her subjects to the institutional review board (IRB) that approved the trial.

In accordance with ICH/GCP guidelines, the Sponsor will inform the Investigator of “findings that could adversely affect the safety of subjects, impact the conduct of the trial or alter the IRB’s approval/favorable opinion to continue the trial.” In particular and in line with respective regulations, the Sponsor will inform the Investigator of AEs that are both serious and unexpected and are considered to be related to the administered product (“suspected unexpected serious adverse reactions” or SUSARs). The Investigator should place copies of these safety reports in the Investigator File. National regulations with regard to safety report notifications to Investigators will be taken into account.

The Investigator will be responsible for promptly notifying the concerned local IRB of any safety reports provided by the Sponsor and of filing copies of all related correspondence in the Investigator File.

#### Methods of Recording Adverse Events in the e-CRF

Complete, accurate and consistent data on all AEs experienced for the duration of the reporting period will be reported on an ongoing basis in the appropriate section of the e-CRF. Among these AEs, all SAEs must be additionally documented and reported using the SAE Report provided at the Initiation visit by the Sponsor or designee,as described in [(see Section 7.9.1.11)](#_Procedure_for_Reporting).

It is important that each SAE Report include a description of the event, its duration (onset and resolution dates/times), its severity, its relationship with the Medicinal Product, any other potential causal factors, any treatment given or other action taken (including dose modification or discontinuation of the Medicinal Product and its outcome. In addition, serious cases should be identified and the appropriate seriousness criteria documented.

As the quality and precision of acquired AE data are critical, Investigators should use the AE definitions provided in the above sections and should observe the following guidelines when completing the AE pages of the e-CRF:

- If a condition is a medical diagnosis, appropriate terminology should be used (e.g., high blood pressure should be reported as hypertension when a confirmed diagnosis exists)
- Any condition which contains more than one unique concept should be split into two or more events, or the condition should be described as a single medical diagnosis or concept (e.g., nausea and vomiting should be listed as two separate entries or as “gastroenteritis” when it is diagnosed as such)
- If a diagnosis is not available then the signs and symptoms should be recorded (e.g. if runny nose and itchy eyes have not been previously diagnosed as hay fever, then runny nose and itchy eyes should be recorded as two separate events)
- Any condition that could have various locations or types should be specified. Examples include:

Pain – left shoulder pain

Ache – generalized body aches or lower backache

Rash – macular rash on lower abdomen

Infection – lower left abdominal injection site infection or, upper respiratory infection; specify genus/species name of infecting organism if known (e.g., E.coli)

- If a subject has a worsening or exacerbation of a pre-existing condition previously reported in the medical history, include the appropriate terminology (i.e., worsening, exacerbation etc.)
- Avoid abbreviations as many abbreviations have more than one interpretation
- Any condition, which is ambiguous, must include additional information. Examples include:

Aches in hands – provide more specificity (i.e., muscle aches or joint aches or general)

Allergy – provide type (i.e., seasonal allergy or allergy to cats)

Angina – provide more specificity (i.e., angina pectoris or angina tonsilaris)

Chest pain – provide more specificity (i.e., musculoskeletal or cardiac or heartburn)

#### Recording Injections Site Reactions in the e-CRF

The most common AEs that may occur at the injection site are the following:

- Injection site redness
- Injection site pain
- Injection site bruising
- Injection site swelling
- Injection site itching
- More rarely, infection, abscess, cellulitis, necrosis

In order to ensure consistency in the reporting of these Injection Site Reactions (ISRs), the investigator is encouraged to use the above terminology, or specify any other type of ISR that the may observe in the course of treatment.

In case ISRs occur after every injection, they should be documented as one event which occurs intermittently during the trial, not as separate events.

#### Recording Flu-Like Symptoms in the e-CRF

The occurrence of flu-like symptoms (FLS) is recognized as a typical reaction to IFN- beta. FLS may include headache, fatigue, fever, chills, myalgia and arthralgia; typically, several of these symptoms would occur concomitantly. If investigators consider the symptoms experienced by the patient as being a FLS, they are encouraged to report the syndrome FLS rather than each individual symptom. If they occur individually, then they should not be reported as FLS. It is important to distinguish between FLS secondary to IFN-beta administration and true symptoms of flu, a viral infection, which would usually not abate within twenty-four hours.

#### Reporting of MS Relapses

In this trial, symptoms of MS relapses or worsening of MS will be recorded in the appropriate section of the e-CRF.

### Pregnancy and In Utero Drug Exposure

Only pregnancies considered by the Investigator as related to study treatment (e.g., resulting from a drug interaction with a contraceptive medication) are considered AEs. However, all pregnancies with an estimated conception date during the period defined in [Section 7.9.1.5](#_Definition_of_Serious) be recorded in the AE section of the e-CRF. The Investigator must notify the Sponsor in an expedited manner of any pregnancy using thePregnancy Report Form (Part I), which must be transmitted according the same process as described for SAE reporting in [Section 7.9.1.11](#_Procedure_for_Reporting)*.*

Investigators must actively follow up, document and report on the outcome of all these pregnancies, even if the subjects are withdrawn from the trial. The Investigator must notify the Sponsor of these outcomes using the Pregnancy Report Form (Part II), and also must complete the SAE Report when the subject sustains an event and the Parent-Child Fetus Report Form when the child/fetus sustains an event.

Any abnormal outcome must be reported in an expedited manner as described in [Section 7.9.1.11](#_Procedure_for_Reporting), while normal outcomes must be reported within forty-five days from the date of delivery.

# Statistics

## Sample Size

The sample size is based on clinical rather than statistical considerations.

## Randomization

This study is not randomized; there is only one treatment group for RRMS patients.

## Analysis Sets

**Intention-to-treat (ITT)**

The ITT Population is the primary analysis population. All RRMS subjects with at least one injection of Rebif® and all HC who have signed the ICF will be included in the ITT Population.

**Per protocol**

The per protocol population includes all subjects who have been treated according to the clinical trial protocol and fulfill the following criteria:

- Compliance with all entry criteria
- Absence of major clinical trial protocol violations with respect to factors likely to affect the efficacy of treatment
- Adequate compliance with trial medication.

**Safety**

The safety population includes all ITT subjects.

## Description of Statistical Analyses

### General Considerations

All statistical tests will be two-tailed and considered significant at an α=0.05 level of significance; all confidence intervals will be two-sided 95% confidence intervals.

Dropouts, if any, will be examined. Subjects who stop the Medicinal Product will be asked to remain in the study and will be analyzed with the intention to treat, but adding a covariate that alternative therapies have been given. Individual data will be analyzed. No imputation of missing data will be performed.

T-tests and chi-square tests for independent samples will be used for comparison of demographic and clinical characteristics between RRMS patients and HC.

VW-MTR and SWI spatial distribution analysis will be conducted directly on the images. Analysis of MRI measures may require a variance stabilizing transformation, if skewness is observed in their assessments. Each of the MRI parameters will be examined and appropriate transformations will be applied, if necessary.

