### Study Subjects

It is estimated that fifty five subjects with RRMS will be screened, to achieve twenty-five intent to treat (ITT) subjects. In addition, 15 HC subjects will be enrolled as a reference group according to the same age range requirements and the same ratio of males to females as the RRMS subjects. It is estimated that the 40 subjects (25 RRMS and 15 HC) will be recruited at one center in the USA.

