### Withdrawal from the Trial

Subjects are free to discontinue the trial at any time without giving their reasons.

Additionally, the Investigator may withdraw a subject from study treatment at any time if considered to be in the subject’s best interest. Withdrawal from study treatment is mandatory in the following situations:

- Pregnancy [(see Section 7.9.2)](#_Pregnancy_and_In)
- Initiation of treatment with an investigational agent or a prohibited concomitant medication [(see Section 6.4.2)](#_Non-permitted_Medicines)
- Initiation of treatment with another (approved or non-approved) disease modifying therapy for MS
- Common Terminology Criteria for Adverse Events (CTCAE) grade IV lab abnormalities or grade IV ‘related’ serious adverse events [(see Appendix C)](#_Appendix_C-_Common_)
- Adverse events leading to prolonged dose reduction of more than two weeks
- Protocol violations, including non-compliance and lost to follow-up
- Intercurrent illness or significant worsening of previous illness
- Administrative reasons
- Withdrawal of the subject’s consent

In case of premature withdrawal from the study treatment, the assessments scheduled for the Week 24/Exit visit should be performed. [(see Section 7.2.2.3)](#_Week_24/Exit_Visit)

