### Non-permitted Medicines

In line with the exclusion criteria in [(see Section 5.4.2)](#_Exclusion_Criteria), subjects may not use any investigational medications or any of the following therapies during the trial:

- Cytokine or anti-cytokine therapy
- Any interferons other than Rebif®
- Intravenous immunoglobulin (IVIg)
- Monoclonal antibodies, mitoxantrone, cytotoxic or immunosuppressive therapy including but not limited to cyclophosphamide, cyclosporin, methotrexate, azathioprine, linomide, teriflunomide, laquinimod, cladribine, total lymphoid irradiation, anti-lymphocyte monoclonal antibody treatment (e.g., natalizumab, alemtuzumab/Campath, anti-CD4)
- Chronic or monthly pulse corticosteroids
- Plasmapheresis
- Glatiramer acetate
- Telbivudine

If the administration of a non-permitted concomitant medication becomes necessary during the trial, the subject should be withdrawn from the trial. [(see Section 5.4.4)](#_Criteria_for_Subject)

Any additional concomitant therapy that becomes necessary during the trial and any change to concomitant drugs must be recorded in the corresponding section of the e-CRF, noting the name, dose, duration and indication of each drug.

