#### Week 24/Exit Visit

**RRMS Subjects**

The following procedures and assessments will be performed at the Week 24/Exit visit or following early termination of a subject from the trial:

- Recording of adverse events and concomitant medications/procedures
- Laboratory Assessments (Chemistry, Hematology, ferritin, transferrin, CBC, LFTs, platelets, uric acid)
- A blood sample will be collected for analysis of thyroid function tests.
- Physical examination unrelated to MS, including height, weight and vital signs [(see Section 7.2.6.1)](#_Physical_Examinations)
- Neurological assessment (full exam, not including EDSS) [(see Section 7.2.6.2)](#_Neurological_Assessments)
- Blood collection for Immunological Samples
- MRI
- For female subjects of childbearing potential, a urine pregnancy test, to be performed locally at the study site
- Reason for termination (if subject terminates early)
- Drug accountability

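### Section 8.4.1 adds a post-baseline alternative-therapy covariate to the ITT analysis; Section 8.4.2 omits it, and the protocol disagrees on whether these subjects stay in the trial

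*Protocol*

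**What the plan says.** **Analysis set.** Section 8.3 makes ITT the primary population: every RRMS subject injected at least once, and every HC who signed consent.

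**Handling of subjects who stop.** Section 8.4.1 (General Considerations) invites anyone who stops Rebif to stay in the study. They are then "analyzed with the intention to treat, but adding a covariate that alternative therapies have been given". Missing data are not imputed.

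**Primary model.** Section 8.4.2 specifies an ANCOVA on ranks with group (RRMS or HC), three-month period, age and gender. No alternative-therapy term is listed. Further covariates appear there only as optional exploratory work.

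**Follow-up after a switch.** Three places bear on this:
- Section 6.4.2, whose list includes other interferons, glatiramer acetate, monoclonal antibodies and mitoxantrone: "If the administration of a non-permitted concomitant medication becomes necessary during the trial, the subject should be withdrawn from the trial".
- Section 5.4.5 makes withdrawal from study treatment mandatory when a prohibited medicine or another disease-modifying therapy is started. It adds: "In case of premature withdrawal from the study treatment, the assessments scheduled for the Week 24/Exit visit should be performed".
- Section 7.2.2.3 has the exit procedures, MRI included, "performed at the Week 24/Exit visit or following early termination of a subject from the trial". Section 5.4.7 seeks the same assessments in anyone who leaves the trial.

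**Design.** "It is estimated that the 40 subjects (25 RRMS and 15 HC) will be recruited at one center in the USA". "This study is not randomized; there is only one treatment group for RRMS patients". "The sample size is based on clinical rather than statistical considerations".

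**The concern.** Starting another therapy happens after treatment begins and may be related to response or tolerability. HC never receive Rebif and so cannot stop it. The indicator can therefore be 1 only in RRMS subjects, and all it does is split that group in two. Its coefficient takes up whatever is particular to the switchers, and the group coefficient is left to describe the rest. An analysis labelled ITT would then count switchers in the set but not in the contrast.

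Two further problems follow from the text. A statistician following 8.4.1 and one following 8.4.2 would fit different primary models. In addition, 8.4.1 plans an analysis of subjects whom 6.4.2, read literally, has removed from the trial. With 25 RRMS subjects and no replacement (Section 5.4.6), each switcher is 1/25 = 4% of the group, so the choice should be settled before the data are seen.

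**Working it through.** The protocol states no power, effect size, SD or switching rate, so there is no planned figure to reproduce. The check is on what the covariate does to the group coefficient.

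**Inputs.** From the protocol: 25 RRMS, 15 HC, and the model terms of 8.4.2. Assumed: k = 1 to 5 switchers among the 25, whose outcome differs from that of other RRMS subjects by d = 0.5 to 1.0 SD.

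**Step 1: algebra without other covariates.** Let g = 1 for RRMS and s = 1 for a switcher. The model y = a + b_g·g + b_s·s has three parameters for three cells (HC, RRMS non-switchers, RRMS switchers), so it reproduces the cell means:
- b_g = mean(non-switchers) − mean(HC)
- b_s = mean(switchers) − mean(non-switchers)
- mean(all RRMS) − mean(HC) = b_g + (k/25)·b_s

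The last line is the contrast for the ITT set. The covariate removes (k/25)·b_s from it.

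**Step 2: the same on ranks.** One simulated data set for each k, ranked over the 40 subjects:

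| k | group effect with covariate | non-switchers − HC | group effect without covariate | all RRMS − HC | (k/25)·b_s |
|---|---|---|---|---|---|
| 2 | 8.98 | 8.98 | 10.29 | 10.29 | 1.32 |
| 3 | 10.28 | 10.28 | 11.15 | 11.15 | 0.86 |
| 5 | 12.03 | 12.03 | 13.17 | 13.17 | 1.14 |

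The identity is exact, as the algebra requires.

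**Step 3: with age, gender and period.** 1,500 simulated trials per setting, two periods, unranked outcome in SD units, true non-switcher effect 0.80, indicator coded per subject:

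| k | d | without covariate | with covariate | switchers deleted | (k/25)·d |
|---|---|---|---|---|---|
| 1 | 0.5 | 0.818 | 0.797 | 0.797 | 0.02 |
| 1 | 1.0 | 0.823 | 0.782 | 0.782 | 0.04 |
| 3 | 0.5 | 0.859 | 0.795 | 0.795 | 0.06 |
| 3 | 1.0 | 0.924 | 0.805 | 0.805 | 0.12 |
| 5 | 0.5 | 0.897 | 0.795 | 0.795 | 0.10 |
| 5 | 1.0 | 1.003 | 0.806 | 0.804 | 0.20 |

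With the covariate, the mean group effect matches deletion of the switchers to within 0.002. In single trials the two differ slightly (SD of the difference at most 0.03), because switchers still inform the age, gender and period terms. The gap between the first two estimates follows (k/25)·d: 0.02 SD at the low end (1/25 × 0.5) and 0.20 SD at the high end (5/25 × 1.0). If d = 0 the expected gap is zero; if k = 0 the covariate has no effect.

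**Step 4: the follow-up rules side by side.** For the same event, the start of a prohibited medicine, 5.4.5 ends study treatment, 6.4.2 ends trial participation, and 8.4.1 wants the subject to stay if Rebif was stopped. Under 5.4.5 and 5.4.7 an exit MRI is still sought, but it may fall well before week 24, whereas the primary endpoint is change from baseline to six months.

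**The case against.** The strongest reply is that 8.4.2, the section devoted to the primary endpoint, omits the covariate, so the primary model may never contain it. The descriptive summaries by group and the within-RRMS signed rank test are also unaffected. This stands as far as it goes: the protocol does not clearly put the covariate in the primary model. But 8.4.1 applies to the analyses generally and attaches the covariate to intention to treat, so the two sections disagree.

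It can also be said that this is a non-randomised pilot, so ITT protects no randomised comparison, and that the protocol expects few or no dropouts. That lowers the severity. It does not remove the mismatch between the named primary set and the contrast estimated.

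A reader might infer several stronger things that the documents do not support:
- *That the covariate biases the result in favour of Rebif.* This assumes that switchers respond worse. The endpoints count both increasing and decreasing voxels against untreated HC, and a smaller RRMS-HC gap is not favourable for both.
- *That the analysis is identical to deleting switchers.* This is exact only without other covariates. If the indicator were coded by period, data from before the switch would still inform the group effect. Subjects who stop Rebif without another therapy stay in it in any case.
- *That other sections remove these subjects altogether.* Only 6.4.2 speaks of leaving the trial; 5.4.5 concerns study treatment, and exit assessments are still sought.
- *That early-exit scans will be analysed as 24-week values.* The shared visit name permits this, but nothing says so, and visit mapping can properly be left to the analysis plan.

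**Conclusion.** The point holds in a limited form. As written, 8.4.1 adds to the ITT analysis a post-baseline variable that can occur only in the RRMS group. If fitted, it turns the group effect into non-switching RRMS versus HC: exactly so without other covariates, and on average with age, gender and period. Sections 8.4.1 and 8.4.2 therefore disagree on the primary model, and 5.4.5, 6.4.2 and 8.4.1 disagree on whether follow-up continues.

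The size cannot be fixed from the protocol. The range of 0.02 to 0.20 SD rests wholly on the assumed 1 to 5 switchers and the assumed shift of 0.5 to 1.0 SD. The direction depends on who switches and on whether increasing or decreasing voxels are analysed. Severity: should fix. The algebra is certain; the practical effect may be nil.

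**What to change.** 1. In 8.4.1, delete the clause that adds the covariate. State that the primary ITT model is the one in 8.4.2, fitted to all available scheduled scans of every treated RRMS subject whatever therapy followed.
2. If the influence of switching is of interest, report a covariate-adjusted or switcher-excluded analysis as a sensitivity analysis, labelled as not ITT, with the number of switchers and the coding of the indicator (per subject or per period).
3. Reconcile 5.4.5, 6.4.2 and 8.4.1 on whether MRI follow-up continues after study drug stops. Which rule applies is for the sponsor and investigator to decide; the sections need to say the same thing.
4. State that an early-exit scan is not counted as a 24-week value.

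The cost is a few sentences and one sensitivity table. The price in interpretation is that the primary contrast will include any effect of the later therapy, which follows from analysing the ITT set as Section 8.3 defines it.
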